▪ Patient is admitted to a nursing home

▪ Development of unstable medical conditions or severe behavioural disturbances as assessed by the physicians of the study centres

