### Sample size

Although the Dutch original randomised control trial [26] found very large effect sizes on the performance scale of the Interview of Deterioration in Daily Living Activities in Dementia (at 12 weeks follow-up d-value = 2.4), the power of the WHEDA-study is calculated conservatively in order to detect small effects. The rationale is the change in design; that there is an active control treatment, less professional experience in the experimental treatment in Germany, less patients per therapist and a longer follow-up in a sample with expected progress in dementia, may reduce the expected effects. The power calculation is based on an analysis of variance of two groups and four measurement time points (since in the postal follow up at 52 weeks the IDDD is recorded, too). Hypothesising an alpha of .05 (two-sided), a power of .80 and a correlation of .7 between four measurement time points, a sample of 84 persons is needed, in order to detect an effect of f = .10 [72]. According to drop out rates of the Dutch study, 280 patients must be screened and 140 recruited (see figure 1).

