### Statistical methods

Data are entered via special MS Access entry masks automatically controlling for data plausibility. In addition, sections of entered data are checked for typing errors by hand, in order to ensure an error rate lower than 0.2%. Baseline measures and demographics of participants significantly differing at baseline in intervention and control group and control measures are used as co-variates in an analysis of variance with repeated measures with two groups and four measurement time points. If the diagnosis of extent and type of missing data reveal that the precondition is given, the Full Information Maximum Likelihood (FIML) method will be applied for data replacement [73]. The primary intention-to-treat analysis, including all participants with valid data (whether they did or did not receive the intervention), will be compared with a per protocol analysis excluding all participants with documented deviations from the protocol (ie. not receiving the entire intervention or receiving an incomplete follow-up). The comparison of these groups will be adjusted for baseline imbalance and process variations. Variations in the adherence to protocol; to the treatment manual and to therapeutic recommendations; variations in medication and progress of cognitive decline as well as variations in the quality of supporting or hindering structures and processes at the study sites are considered as possible mediators. All statistical tests will be two-sided on an alpha level of .05.

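### FIML is used only if an undefined data check is passed; if that check concerns missing at random, observed data cannot settle it, and the only other analysis named is a four-occasion repeated-measures ANOVA

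*Protocol article*

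**What the plan says.** Under Statistical methods, the article specifies a repeated-measures analysis of variance with two groups and four measurement times, with covariates. FIML enters only under a condition: "If the diagnosis of extent and type of missing data reveal that the precondition is given". The article does not say what the precondition is, or what is done if it is not met. It describes FIML as a way of replacing data.

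The main analysis set is described as "The primary intention-to-treat analysis, including all participants with valid data (whether they did or did not receive the intervention". It is compared with a per-protocol set that leaves out patients who did not receive the whole intervention or whose follow-up was incomplete.

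Under Sample size, "a sample of 84 persons is needed, in order to detect an effect of f = .10". Then, with reference to dropout in the Dutch trial, "280 patients must be screened and 140 recruited".

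Under Participants, the discontinuation criteria are death of patient or caregiver, "Patient is admitted to a nursing home", and development of an unstable medical condition or severe behavioural disturbance.

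**The concern.** FIML is valid when data are missing at random: given what was observed, loss does not depend on the values not seen. Observed data can give evidence against missing completely at random. They cannot separate missing at random from missing not at random. A check of the type of missingness therefore cannot confirm the assumption on which FIML rests. If that is the check intended, the primary method is chosen by a test that cannot answer its question.

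If the condition fails, all that remains in the text is the four-occasion ANOVA on patients with valid data. In its classical form it drops anyone lacking a visit and generally needs a stronger missing-data assumption than FIML. The rule could then move to the more fragile method when missing data look most troublesome.

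In that branch, the intention-to-treat set would also lose patients with incomplete follow-up. Comparing it with the per-protocol set would then say little about attrition bias, although the two sets would still differ over patients who did not receive the entire intervention.

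**Working it through.** **1. The plan's own sample size.** Inputs from Sample size: "Hypothesising an alpha of .05 (two-sided), a power of .80 and a correlation of .7 between four measurement time points", effect f = 0.10, two groups, four times. For the group-by-time interaction with sphericity:

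- λ = f²·N·m/(1−ρ) = 0.01 × 84 × 4 / 0.3 = 11.2
- df1 = (2−1)(4−1) = 3; df2 = (84−2) × 3 = 246
- Power = 0.805 at N = 84 and 0.794 at N = 82, so 84 is reproduced.

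**2. Implied loss.** 1 − 84/140 = 0.40, and 84/(1−0.40) = 140 exactly. The 40% is derived; the article prints no percentage, and the flow chart is not available. If all 56 losses were dropped, 84 of 140 (60%) would be analysed, with power still 0.805. With all 140 complete, power would be 0.964. A likelihood analysis that uses partial data lies between these two values.

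**3. Bias, illustrative simulation.** Assumptions: unit-variance scores, correlation 0.7 at all times, no true effect. At each visit, dropout has logit −1.75 + s × previous score, with slope s set by arm, so data are missing at random. There were 20 runs of 20,000 patients per arm. Between 57% and 62% completed, i.e. 38% to 43% were lost. Arm difference in change from baseline to last visit, in SD:

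| s, intervention / control | Completers only | Likelihood |
|---|---|---|
| 0 / 0 | −0.003 | −0.004 |
| 1 / 1 | −0.005 | −0.004 |
| 0.5 / 1 | −0.020 | 0.000 |
| 0 / 1 | −0.044 | −0.003 |
| 1 / 0 | 0.040 | −0.001 |
| 1 / −1 | 0.086 | 0.002 |

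Completers show essentially no bias when loss works alike in both arms, and about 0.02 to 0.09 SD when it does not. Likelihood estimation stays within 0.005 SD of zero.

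**4. Precision.** Take ρ = 0.7 and adjust for baseline. The residual variance per visit is 1 − 0.7² = 0.51, and the residual covariance is 0.7 − 0.7² = 0.21. For the mean of weeks 6, 16 and 26:

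- 84 completers (42 per arm): variance per patient = (0.51 + 2 × 0.21)/3 = 0.31; SE = √(2 × 0.31/42) = 0.1215.
- Add 14 patients seen through week 16 and 14 seen at week 6 only (assumed; 7 of each per arm). Summing the information matrices gives SE = 0.1095.
- Variance ratio (0.1095/0.1215)² ≈ 0.81, a reduction of about 19%; 84/0.81 is about 103 completer-equivalents.
- Range: no partial data gives 84; all 56 seen through week 16 gives 128.
- For week 26 alone, the same 14 + 14 split gives a variance ratio of about 0.95, a gain of about 5%.

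**The case against.** The strongest reply is that the article does not prescribe a complete-case analysis. A reader might infer that failing the check means a completers' analysis labelled intention-to-treat, but the text is silent on that branch, and multiple imputation or another method would be equally compatible with it. The precondition might concern the extent of missing data rather than its mechanism; if little were missing, omitting FIML would do little harm. An unnamed alternative and sensitivity analyses are also details that an article commonly leaves to the full protocol or analysis plan. All of this stands, and it limits the point to the condition itself, which the article does fix.

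Other tempting readings also go too far:

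- **A stated 40% loss.** The figure is only implied, and the split of causes among the 56 is unknown.
- **A trial short of power.** The stated 84 completers still give 0.805.
- **Bias whenever loss rates differ.** Unequal rates alone do not bias the comparison; loss must also relate to outcome.
- **A hidden benefit of about 0.10 SD.** Assuming 15% against 5% nursing-home loss and patients 1 SD worse gives (0.15 − 0.05) × 1 = 0.10 SD. Every input is assumed. The figure compares completers with unobserved full data, and if loss is not at random a likelihood model also misses part of it. It does not measure the harm done by the condition.

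**Conclusion.** The point holds in limited form. The article makes its missing-data method depend on an undefined check. If the check is for missing at random, no diagnosis of the observed data can settle it. This is a rule stated badly rather than a detail left out.

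The discontinuation criteria make a link between loss and functioning plausible. Whether that link differs by arm, and hence the size of any bias, is unknown; 0 to 0.09 SD is an illustration under assumed dropout models. The precision gain (19% for the three-visit mean, 5% for week 26) rests on an assumed pattern of partial data and disappears if there are none. Both figures describe the branch in which FIML is not used and only completers are kept, which is inferred. The change is worth making because it is nearly free and removes a data-driven choice of the primary estimator.

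**What to change.** State that the primary analysis is a mixed model for repeated measures, or equivalently FIML, on all randomised patients with any IDDD value. Remove the condition. Delete the wording that presents FIML as replacing data: it uses the observed values and imputes nothing.

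Optionally, prespecify one sensitivity analysis for data missing not at random, with death handled separately. This is an addition rather than the correction of an error.

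The cost is a change of wording and a small amount of extra analysis work. No new data are needed.

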### Randomisation

After the recruitment of an individual, the physician of the study centre e-mailed the request of randomisation to a statistician at a distant site. The physician also informed the assessor (and optionally a co-ordinator of the study centre) and asked him/her to schedule all assessment dates according to the protocol. After the referral by the centre physician, the independent statistician allocated the individual to COTP or COTC. The randomisation sequence was computer-generated with blocking by centre and groups of two persons, without stratification and in a ratio of 1:1. Group allocation was e-mailed to the therapists at the study centre. The therapists decided who would be responsible for this case and the lead therapist confirmed reception of group allocation to the independent statistician. In addition, the lead therapist informed his centre team that he had received group allocation. In order to avoid any contamination, the centre therapists must schedule treatment sessions on their own. He/she also has to fax the records to the WHEDA-headquarters and retain their records, strictly separated from any other centre staff. Masking of patients and caregivers is not possible due to the different quantity of home visits between intervention and control group. Assessors might be contaminated by hints of patients or caregivers during the assessments at home. Assessors, patients and caregivers are asked to avoid any talks about the treatment. The extent of assessor 'blinding' will be evaluated by the comparison of actual group assignment and the assessor's estimation of group assignment. The procedure of video-rating ensures the full 'blinding' of the Dutch raters of an individual's assignment to group. Independent staff of the WHEDA-headquarters check and 'clean' the videotapes from any hint of group assignment or personal data, before the tapes are transferred to the Netherlands.

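### FIML is described as a way to replace missing data beside a repeated-measures ANOVA; taken literally, filled-in IDDD values would be analysed as if observed

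*Protocol article*

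**What the plan says.** The Statistical methods section names one analysis, with covariates: "an analysis of variance with repeated measures with two groups and four measurement time points". It handles missing data in one conditional sentence. The condition is "If the diagnosis of extent and type of missing data reveal that the precondition is given"; the action is that "the Full Information Maximum Likelihood (FIML) method will be applied for data replacement". The same section defines the primary intention-to-treat set as everyone with valid data, whether or not they received the intervention.

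The Sample size section gives the planning figures: "Hypothesising an alpha of .05 (two-sided), a power of .80 and a correlation of .7 between four measurement time points", and "a sample of 84 persons is needed, in order to detect an effect of f = .10". The recruitment target follows: "According to drop out rates of the Dutch study", the plan is that "280 patients must be screened and 140 recruited". No dropout rate is printed.

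**The concern.** FIML maximises the likelihood of the values that were observed. Its output is estimates and standard errors, not a completed data file. A standard repeated-measures ANOVA, by contrast, needs a value at every visit for every participant it uses. An analyst who follows the two statements as printed would fill the gaps from a likelihood fit and then run the ANOVA on the completed file.

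The harm depends on a choice that the sentence leaves open.

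- **Arm in the fill-in model.** The effect estimate is unbiased. But the filled values add no information while counting as full observations, and conditional means also carry no residual scatter. Standard errors are too small and the test rejects too often.
- **Arm not in the fill-in model.** Filled values are drawn towards a mean common to both arms. The test level holds, but a real effect is diluted.

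The affected result is the primary one: change in IDDD over the post-intervention visits.

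**Working it through.** **1. The plan's own sample size.** For the group-by-time interaction, λ = N·f²·m/(1 − ρ), with 3 and 3(N − 2) degrees of freedom. With N = 84, f = .10, m = 4 and ρ = .7: λ = 84 × .01 × 4 / .3 = 11.2, on 3 and 246 df. Power is .805, so the stated 84 is reproduced. A between-groups main effect would need 612, so the interaction is what the trial was sized on, and it is the test examined here.

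**2. Implied loss.** 1 − 84/140 = 40% of participants. This is an inference. It is also not a share of values:

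- Assumed staged loss of 15, 28 and 40% at weeks 6, 16 and 26: (0 + 15 + 28 + 40)/4 = about 21% of all values, and (15 + 28 + 40)/3 = about 28% of post-baseline values.
- All 56 leavers gone right after baseline: 56 × 3 = 168 of 560 values (30%), or 168 of 420 post-baseline values (40%).

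**3. Type I error of the group-by-time F test.** From the article: 140 participants, 1:1 allocation, four visits, correlation .7, nominal level .05. Assumed: normal data, equal correlations, loss completely at random. Gaps are filled once from a maximum-likelihood (EM) fit, and the ordinary uncorrected ANOVA is then run (1,000 to 2,000 simulated null trials per setting).

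| Loss by week 26 | Timing | Arm in fill-in | Arm not in fill-in |
|---|---|---|---|
| 40% | staged | .22 to .27 (conditional mean), .17 (random draw) | about .05 |
| 40% | all after baseline | .38 (conditional mean), .27 (random draw) | about .05 |
| 20% | staged | .12 (conditional mean), .11 (random draw) | .04 to .05 |
| 20% | all after baseline | .17 (conditional mean), .16 (random draw) | about .05 |
| 10% | either | about .09 | about .05 |

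With correlation .5 the staged 40% figures are .22 and .18. The group main effect is less affected: .06 to .11 at 40% loss with arm in the fill-in model.

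**4. Why it inflates.** With the 15/28/40% pattern and arm in the fill-in model, the week-26 contrast has a reported standard error of .109 against a true .157. The nominal cut-off of 1.96 then acts as 1.96 × .109/.157 = 1.36. The two-sided normal tail beyond 1.36 is about 17%, which agrees with the simulated 17%.

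**5. Dilution when arm is left out.** With a true week-26 effect of .40 SD and 40% staged loss, the mean estimate is .29, that is (.40 − .29)/.40 = 27% too small. A bound makes this plausible. If filled values carried no arm difference, the estimate would be .6 × .40 = .24; earlier observed visits restore part of the gap. At 20% loss the same bound is .8 × .40 = .32, and the estimate is about .36. The exact figures depend on the staging and on the effect at earlier visits.

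**6. Likelihood fitted directly to the observed values.** Under staged loss the null rejection rate is .05 and the .40 effect is recovered without bias. In the harsher setting, with 40% lost right after baseline, an uncorrected chi-square likelihood-ratio test rejects about .07 (500 runs, Monte Carlo standard error about .01).

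**The case against.** The strongest reply is that the faulty procedure is inferred from two loose words. The article does not say that values are filled in once, that filling comes before the ANOVA, or that filled values count in the error degrees of freedom. It names FIML, and an intention-to-treat set of participants with valid data fits estimation from observed values better than a completed file. On that reading the test is near nominal. This stands: it rules out saying that the plan commits to single imputation. It does not rescue the sentence, which assigns FIML a task it does not perform and pairs it with an analysis that cannot use incomplete rows.

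A second reply is that FIML is conditional on a diagnosis that covers the extent of missing data, so the heaviest loss might never reach this step. That also stands, and it is a reason to quote a range that includes 20% loss and below.

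A third is that a condensed article may leave the variables in the missing-data model, and the handling of uncertainty, to a full plan. Agreed; their absence is not the point. The point is a stated rule that is wrong as printed.

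A reader might infer that 40% of the values would be invented. The documents do not support this: 40% is an implied share of participants, and under staged loss about 21% of all values would be missing.

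**Conclusion.** The missing-data rule is badly stated and should be corrected before the primary analysis. Its consequence is conditional. Under single fill-in with arm in the model, and random staged loss reaching 20 to 40% of participants by week 26, the group-by-time type I error is about 11 to 27%; it reaches about 38% only if 40% are lost right after baseline. With arm omitted the level is near 5%, and the cost is a week-26 estimate of about .29 to .36 in place of .40 SD. These figures rest on an assumed loss pattern, loss completely at random, and correlation .7.

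Two stronger conclusions are tempting and not supported. One is a single false-positive rate of about 25%: that is one scenario within a range of roughly 5 to 38%, set by choices the article does not make. The other is that the primary result is wrong on any reading: if direct FIML estimation was intended, the test is close to nominal and the error lies in the description of the method and of the analysis model.

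**What to change.** Delete the words about data replacement and state the following: *Missing values are not replaced. The primary IDDD analysis is a likelihood-based repeated-measures model with arm, visit and arm-by-visit terms and an unstructured covariance, fitted to all observed values and keeping the planned covariates.* This replaces the ANOVA as the named primary analysis and settles both readings.

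Where a completed file is needed, for example to build a score, use multiple imputation with arm in the imputation model and combine the results by Rubin's rules. Do not run the ANOVA on a singly filled file.

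The cost is wording only; no new data or visits are needed. Intervals will be somewhat wider than after a single fill-in, because they carry the uncertainty that filling in would hide.

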## Discussion

The WHEDA-study evaluates whether the improved effects on daily functioning in people with dementia, found in a Dutch RCT within a community occupational therapy programme, can be replicated in a single blind German randomised controlled multi-centre design with prolonged follow-up assessment. The transfer from the Dutch mono-centre design to the pragmatic multi-site trial in a German context implicated several determinations in design issues.

 1. The decision for a multi-centre design is justified by a short time frame for recruitment and the necessity to anticipate the variability of contexts possibly given later when the intervention might be delivered in routine care.

 2. An active control intervention is applied, since a consultation on how to deal with the consequences of the disease is normal in outpatient dementia care in Germany and the WHEDA-study aims at the evaluation of potential effects additional to standard care. Furthermore waiting group control conditions may lead to disappointment and feelings of neglect in the waiting group after randomisation and may enhance the contrast between intervention and waiting group.

 3. The follow-up period is prolonged from 12 weeks in the Dutch trial to 26 weeks in the WHEDA study, in order to assess the long-term treatment potential to reduce the negative consequences of cognitive decline in everyday functioning. The additional one-year follow-up intends to evaluate the impact of interventions on the incidence of nursing home placements.

 4. The Assessment of Motor and Process Skills (AMPS) used in the original Dutch study was replaced by the PRPP, since AMPS was not available in Germany and the PRPP shows better feasibility. Since PRPP pilot data are not available, the power calculation was based on the IDDD.

 5. The 14 German occupational therapists with a minimum of one year's experience in the treatment of people who are cognitively impaired, undertook a 16 hours post-graduate skills training course and exercise their skills in training on the job for about 35 hours within the WHEDA pilot phase. The two Dutch occupational therapists had four years experience in the treatment of people who were cognitively impaired and each had 240 hours of experience in treatment according to the guidelines after post-graduate skill training course of 80 hours. The WHEDA recruitment period of nine months is shorter than in the Dutch trial which had three years and nine months recruitment time. The reduced recruitment period, the extended number of involved therapists and the shortened seminar time all match routine conditions, which would be found in an implementation of standard dementia care.

 6. The WHEDA study does not determine stable medication for people with dementia as inclusion criteria, since changes in medication are common in dementia care. In contrast to the Dutch original trial, the WHEDA study is kept open to patients, for whom occupational therapy goals cannot be defined before the start of the treatment. This is congruent to the routine situation, since German physicians cannot explore possible occupational therapy goals before prescribing this treatment.

According to the arguments listed above, effects as revealed by the Dutch original study may be reduced in the multi-centre prolonged WHEDA design. For this reason, the statistical power was calculated conservatively and a process evaluation assessing variations in settings and delivery processes as well as treatment fidelity and adherence to therapeutic recommendations was planned. Adjusted analyses considering the variations in settings, structures and processes should be able to provide explanations for outcomes differing between the Dutch original study and the German replication.
